**Secondary endpoints**
Key secondary endpoint
Total eGFR slope during the 104-week study period
Efficacy endpoints
Change from baseline in the following items at each visit
Lipid metabolism^a^
TG, HDL-C, TC, LDL-C, non-HDL-C, TG/HDL-C, and TRL-C
Kidney function
eGFR, Cr, UPCR, UACR, and predicted ACR^b^
Change in proportion of CKD stages between baseline and 104-week visit
Proportion of CKD stage transition between baseline and 104-week visit
Liver function
AST, ALT, γ-GTP, and ALP
Others
CK, BUN, uric acid, total protein, albumin, CRP, RBC, WBC, blood glucose^a^, Hb, Hct, platelet count, HbA1c (diabetic patients only), BNP (NT-proBNP) (heart failure patients only)
Outcomes
Incidence of composite kidney events, and components of kidney events
Incidence of composite CVEs, and components of CVEs
Incidence of rhabdomyolysis
Incidence of acute kidney injury
Physical findings
Body weight, body mass index, blood pressure (rest sitting position), pulse rate
Exploratory items
eGFR-cys, and cystatin C
Comparison of eGFR slope before the study and during the study^c^
Change from baseline in the above items at each visit and 8 weeks after 104-week visit in the cases with data available
Correlation between change in TG and other variables
Safety evaluation
Incidence of severe AEs
Incidence of AEs
Incidence of severe side-effects related to the study drug
Incidence of side-effects related to the study drug

a Lipid metabolism-related items and blood glucose analyzed separately for fasting and non-fasting blood samples.

b predicted ACR = exp 5.2659 + 0.2934 × log [min (PCR/50, 1)] + 1.5643 × log {max [min (PCR/500, 1), 0.1]} + 1.1109 × log [max (PCR/500, 1)] − 0.0773 × (if female) + 0.0797 × (if diabetic) + 0.1265 × (if hypertensive).

c eGFR slope during the study includes both chronic and total eGFR slopes. ACR, albumin-to-creatinine ratio; ALP, alkaline phosphatase; ALT, alanine aminotransferase; AST, aspartate aminotransferase; BNP, brain natriuretic peptide; BUN, blood urea nitrogen; CK, creatine kinase; Cr, creatinine; CRP, C-reactive protein; CVE, cardiovascular event; eGFR-cys, eGFR based on cystatin C; γ-GTP, gamma-glutamyl transpeptidase; Hb, hemoglobin; HbA1c, hemoglobin A1c; Hct, hematocrit; HDL-C, high-density lipoprotein cholesterol; LDL-C, low-density lipoprotein cholesterol; NT-proBNP, N-terminal pro BNP; RBC, red blood cell count; TC, total cholesterol; TRL-C, TG-rich lipoprotein cholesterol; WBC, white blood cell count.

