### Statistical analysis

#### Sample size

On the basis of a previous study [20] and a guideline [21], a difference of 0.5–1.0 ml/min/1.73 m^2^/year in eGFR slope has been shown to be associated with a >97.5% probability that the drug will also reduce the risk of kidney failure. Therefore, we defined a difference of 0.5 ml/min/1.73 m^2^/year in eGFR slope between the study groups as a non-inferiority margin, assuming that the standard deviation (SD) would be 4.0 [22]. This SD estimate was based on a previous study of Japanese patients with type 2 diabetes and renal dysfunction [22]. This estimate was considered appropriate because it was derived from clinic-based real-world data in Japan, which closely reflects the multicenter clinical setting and patient characteristics of the present study. Moreover, because the JKAPI-CKD study applies rigorous inclusion and exclusion criteria (e.g. eGFR ≥20 and <60 ml/min/1.73 m² and exclusion of severe proteinuria), the study population is expected to be more homogeneous than general real-world cohorts, further supporting the validity of this assumption. The target enrollment of 2200 participants was calculated to detect a difference in the primary endpoint of 0.5 ml/min/1.73 m^2^/year eGFR slope difference with a power of 80% and an alpha error of 2.5%, accounting for a potential 10% drop-out rate.

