#### Efficacy analysis

The annual rate of change in eGFR from 12 to 104 weeks (chronic eGFR slope) will be analyzed using a random coefficient model. In this model, fixed effects comprise the treatment group, observation time point, and the interaction between the treatment group and observation time point; random effects comprise the intercept and observation time point. Chronic eGFR slope will be compared between the treatment and control groups in the following order: (i) the non-inferiority of the pemafibrate group to the control group will be examined. Non-inferiority will be concluded if the lower limit of the 95% confidence interval (CI) for the eGFR slope in the pemafibrate group compared with the control group is >−0.5. (ii) The superiority of the pemafibrate group will be examined if non-inferiority is achieved. The difference will be considered statistically significant when the lower limit of the 95% CI for the eGFR slope in the pemafibrate group compared with the control group is >0.0. Randomization will be stratified by age, baseline eGFR category, diabetes status, and hypertension status. These stratification factors will be adjusted as covariates in the primary analysis model because they are established predictors of eGFR decline and are expected to reduce residual variance.

The annual rate of change in eGFR during the 104-week study period (total eGFR slope) will be analyzed using the same procedure as that for chronic eGFR slope. Regarding changes in other variables, the least-squares mean, and its 95% CI for each visit will be calculated using the mixed-effects models for repeated measures, and differences between the groups will be calculated. Comparisons between the groups will be performed using the unpaired *t*-test. The proportions of participants in each CKD stage and grade of urinary protein qualitative evaluation will be evaluated using the Chi-square test. Regarding the outcome measures, the incidence rates will be calculated using the person-year method, and survival curves will be confirmed using the Kaplan–Meier method. When adjusting for covariates, a Cox proportional hazards model will be used to calculate hazard ratios. Stratified analyses will be performed for the endpoints, such as by fasting or non-fasting status, medical history, or concomitant medications. Sensitivity analysis will also be performed to adjust for potential confounding factors, such as sex or UACR at enrollment.

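### The Chi-square test fixed for CKD stage and urinary protein grade is valid but ignores category order and, on week-104 stage, the baseline stage; at the planning effect an ordinal test using baseline has two to three times the power

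*Protocol article*

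**What the plan says.** Table 2 of the protocol article lists two stage outcomes among the non-key secondary endpoints for kidney function: "Change in proportion of CKD stages between baseline and 104-week visit" and "Proportion of CKD stage transition between baseline and 104-week visit". Both refer to baseline. The Efficacy analysis section then fixes the test: "The proportions of participants in each CKD stage and grade of urinary protein qualitative evaluation will be evaluated using the Chi-square test". For these outcomes it names no trend or ordinal method, no baseline term and no stratification. It does not say which of the two stage endpoints the test serves. Covariate adjustment is stated for the primary slope model, and a Cox model is named for events. Qualitative urinary protein grade does not appear under that name in Table 2.

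No power is stated for any stage or protein outcome. The only planning figures are those for the slope, in the Sample size section: "The target enrollment of 2200 participants was calculated to detect a difference in the primary endpoint of 0.5 ml/min/1.73 m^2^/year eGFR slope difference". That section sets power at 80% and alpha at 2.5%, allows 10% for drop-out, and assumes an SD of 4.0.

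**The concern.** CKD stages and protein grades are ordered. A Pearson Chi-square gives the same statistic if the columns are shuffled, and it spreads a shift in one direction over several degrees of freedom. Entry is restricted to eGFR from 20 to below 60, so where a participant starts largely determines the stage at two years. A test on week-104 stage alone leaves that between-person variation in the noise. The protocol uses the opposite reasoning for its primary model, which is adjusted for the stratification factors, including baseline eGFR category, to reduce residual variance.

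At stake is the chance of seeing a real difference in stage, in either direction, in a non-key secondary outcome. The validity of the test is not in question.

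**Working it through.** **1. Reproduce the plan's own figure.** Per arm, n = 2(1.960 + 0.842)² × 4.0² / 0.5² ≈ 1005, or 2010 in total. Allowing 10% drop-out gives 2010/0.9 = 2234, or 2010 × 1.1 = 2211. The stated 2200 is within 3% of both. It leaves 2200 × 0.9 / 2 = 990 evaluable per arm.

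**2. Inputs to the simulation.**
- From the documents: 990 per arm; slope difference 0.5/year, also 0.75 and 1.0 (the cited range is 0.5 to 1.0); slope SD 4.0/year; baseline eGFR 20 to 60; 104 weeks; randomization stratified at eGFR 45.
- Assumed: baseline eGFR uniform on 20–60, or normal with mean/SD 45/10 or 42/12 truncated to 20–60; mean decline 2/year; normally distributed change; SD of the two-year change 4.0 × 2 = 8; stage cut-points 60, 45, 30 and 15.

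**3. Model and tests.** Week-104 eGFR = baseline − 4 + 2 × (slope difference) × arm + error, then cut into stages. There were 1500 simulated trials per setting, tested at two-sided 5%. The tests were (a) Pearson Chi-square on the arm-by-stage table; (b) a rank test without baseline; (c) a rank-score test adjusted for baseline stage. Relative loss = 1 − power(a)/power(c).

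| Difference/year | Baseline eGFR | (a) Chi-square | (b) Ordinal, no baseline | (c) Ordinal with baseline stage | Loss |
|---|---|---|---|---|---|
| 0.5 | uniform | 0.161 | 0.227 | 0.565 | 72% |
| 0.5 | 45/10 | 0.212 | 0.384 | 0.573 | 63% |
| 0.5 | 42/12 | 0.189 | 0.341 | 0.591 | 68% |
| 0.75 | uniform | 0.397 | 0.602 | 0.910 | 56% |
| 0.75 | 45/10 | 0.565 | 0.794 | 0.915 | 38% |
| 0.75 | 42/12 | 0.499 | 0.743 | 0.912 | 45% |
| 1.0 | uniform | 0.725 | 0.882 | 0.995 | 27% |
| 1.0 | 45/10 | 0.849 | 0.956 | 0.988 | 14% |
| 1.0 | 42/12 | 0.807 | 0.949 | 0.995 | 19% |

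Without stratified randomization, the 0.5/year powers were 0.20–0.27 for (a) and 0.58–0.59 for (c), a loss of 54–66%. Further runs with a rank test stratified by baseline stage put that test at up to about 0.60 at 0.5/year. They widened the ranges of loss to 38–58% at 0.75/year and 14–32% at 1.0/year.

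**4. Order and baseline separately.** At 0.5/year with stratified randomization, (a) against (b) gives 1 − 0.161/0.227 = 29% to 1 − 0.212/0.384 = 45%. The rest of the gap comes from using baseline stage.

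**5. The transition reading.** Suppose the Chi-square is applied to worsened/same/improved. Its power at 0.5/year is 0.46–0.49, against about 0.58 for an ordinal test on the same categories. For example, 1 − 0.487/0.583 = 16%; the loss is about 16–20%.

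**6. Sensitivity at 0.5/year.** With SD of change 5 the powers are 0.26–0.33 versus 0.79–0.81. With SD 10 they are 0.17–0.20 versus 0.45–0.46. With stages merged to three categories they are 0.295 versus 0.562 (48% lost). Mean declines of 1 and 3/year gave the same picture.

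**7. Type I error.** With no difference between arms, the Chi-square rejected in 4.5–4.9% of trials and the baseline-adjusted test in 4.1–4.3%.

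**The case against.** The strongest reply is that nothing here is stated wrongly. An arm-by-category Chi-square keeps its type I error, the outcome is not a key endpoint, and the article may simply condense a fuller analysis plan. Stage is eGFR cut into bands, and eGFR itself is analysed by the slope models and by mixed models at each visit, with kidney events analysed separately. All of this stands, and it limits the consequence. It does not make an unordered, unadjusted test preferable. The test is also named in the text, so it is not a detail left open.

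Three stronger readings are tempting, and the documents do not support them:
- A reader might infer that over half the power is lost in general. That holds at 0.5/year on week-104 stage, against a comparator using both order and baseline. It does not hold at 1.0/year or for transition categories, which already use the baseline stage.
- A reader might infer that baseline and week-104 records will be pooled, counting each person twice. The preceding sentence in the Efficacy analysis section is about comparing the groups, so a between-arm test is the natural reading, and nothing says that records will be pooled.
- A reader might infer that a true kidney effect would be missed. The continuous eGFR analyses would test it with more information.

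Nor is the ordinal approach without drawbacks; they are given with the change below.

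**Conclusion.** The concern holds as a point of efficiency. At the planning values, power on week-104 stage is about 0.16–0.27 with the planned test and about 0.57–0.60 with an ordinal test that uses baseline stage. The advantage shrinks as the true difference grows, and it is modest if the test is meant for transitions.

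These figures rest on a baseline eGFR distribution, a mean decline and a normal two-year change with SD 8 that the documents do not give. The range over those assumptions is part of the result. For urinary protein grade no distribution is available and no loss can be computed; the argument there rests on ordering and baseline alone. The primary and key secondary slope analyses are unaffected. This is worth doing because it is cheap, and it is not a defect that threatens the trial.

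**What to change.** Replace the sentence on the Chi-square test with one saying that week-104 CKD stage and urinary protein grade will be compared between arms in one of two ways: a rank test stratified by baseline category (van Elteren), or a proportional-odds model adjusted for baseline category and the stratification factors. Choose one as the main test. Keep the stage proportions and the baseline-to-week-104 transition table as description, by arm.

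The cost is one sentence and routine code, with no new data or visits. The small downside is that the odds ratio assumes proportional odds, while the rank test avoids that assumption but gives no direct difference in proportions; the descriptive tables supply that. The trial is open-label, so the change should be dated before any comparison of these outcomes by arm.

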### Safety analysis

The safety analysis will be performed using data for the safety analysis set population. AEs during the study period will be summarized using frequency counts and percentages, with 95% CIs calculated by the Clopper–Pearson method. Serious AEs and treatment-related AEs will be summarized similarly. All AEs will be graded for severity in accordance with the Common Terminology Criteria for Adverse Events, version 5.0.

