### Registration and randomization

Investigators will obtain written consent from the participants after confirming that the eligibility criteria are met. This study will use an online electronic data capture system (Viedoc™ version 4 (Viedoc4); Viedoc Technologies AB, Uppsala, Sweden). Investigators will register participants using the Viedoc4 web registration system. Viedoc4 assigns a research number and treatment group for each participant. Eligible participants will be randomly allocated to the pemafibrate or control groups in a 1:1 ratio. Age (<65 years vs. ≥65 years), eGFR (<45 ml/min/1.73 m^2^ vs. ≥45 ml/min/1.73 m^2^), presence/absence of diabetes, and presence/absence of hypertension are the stratification factors because these are involved in the extent of eGFR changes.

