### Treatment

#### Study treatment

Pemafibrate (immediate-release tablet or extended-release tablet) will be administered orally in the pemafibrate group within 8 weeks after enrollment. Patients in the pemafibrate group will receive pemafibrate 0.1–0.4 mg daily for 104 weeks in accordance with the latest instructions on the package insert. The pemafibrate dosage will be adjusted to achieve the TG target (serum TG level <150 mg/dl (fasting) or <175 mg/dl (non-fasting)). The maximum pemafibrate dose is 0.4 mg daily; dose reduction may be considered in patients with hepatic or kidney dysfunction. The maximum pemafibrate dose is 0.2 mg daily for patients with eGFR <30 ml/min/1.73 m^2^. In the control group, conventional treatment will be continued, with observation initiated within 8 weeks after enrollment. With rapid exacerbation of kidney function (i.e. increase in serum creatinine to ≥1.5 times the baseline value or decline in eGFR of ≥40% from baseline), marked increase in creatine kinase (≥5× the upper limit of normal), or myoglobinuria (reddish-brown urine) during the study period, pemafibrate dose reduction or discontinuation will be considered in the pemafibrate group. Investigators are advised to follow local or international practice guidelines to optimize kidney protective treatment.

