#### Follow up

The study schedule is summarized in Supplementary Table 1. Follow-up visits are scheduled at 12 and 26 weeks and then every 26 weeks until 104 weeks. After 104 weeks of observation, participants in the pemafibrate group will stop taking pemafibrate and continue conventional therapy, and will be assessed 8 weeks after discontinuation. Participants in the control group will continue conventional treatment and will be assessed 8 weeks after the 104-week visit. Adherence to study treatment will be assessed by asking participants about missed doses. Blood pressure, pulse rate, and body weight measurements will be obtained at each visit. Blood and urine laboratory tests will also be performed at each visit. Laboratory parameters will be assessed using routine methods in participating medical facilities. In principle, fasting blood samples will be collected (≥10 hours after the last meal). If non-fasting blood samples are collected at baseline, non-fasting blood samples will also be collected during follow up. Details of the laboratory measurements are shown in Supplementary Table 2. LDL-C (direct method) and cystatin C will also be measured if possible (i.e. with insurance coverage). LDL-C (calculated), non-HDL-C, TG/HDL-C ratio, small dense LDL-C, TG-rich lipoprotein cholesterol, eGFR, and eGFR based on cystatin C (eGFR-cys) will be calculated using the formulas described in the Supplementary Methods (Supplementary File 2). Urinalysis will be performed on spot urine samples to assess UACR, if possible (i.e. with insurance coverage), or UPCR. At each visit, concomitant medications, cardio-kidney events, and adverse events (AEs) will be verified by the investigators.

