#### Analysis set

Three analysis populations are defined for this trial: (i) the full analysis set (FAS), defined as all eligible participants who received at least one dose of the study treatment and had at least one observation in the protocol therapy period for the analysis endpoint; (ii) the per-protocol set, defined as participants in the FAS, without significant violation of the study protocol; and (iii) the safety analysis set, defined as participants who received the study drug at least once. The main efficacy analyses will be performed using the FAS population data.

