## CONCLUSION

The JKAPI-CKD study will evaluate the efficacy and safety of pemafibrate use in patients with hypertriglyceridemia complicated by CKD.

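### As written, the safety analysis gives no pemafibrate-versus-control estimate for general and serious adverse events: only one-sample intervals, on a safety set defined by receipt of the study drug

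*Protocol article*

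**What the plan says.** The Safety analysis section of the protocol article specifies that "AEs during the study period will be summarized using frequency counts and percentages, with 95% CIs calculated by the Clopper–Pearson method". It adds: "Serious AEs and treatment-related AEs will be summarized similarly". It names no risk difference, ratio, rate comparison or test, and it does not say that the summaries are by arm.

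On the population, the same section says: "The safety analysis will be performed using data for the safety analysis set population". Under Analysis set this is "the safety analysis set, defined as participants who received the study drug at least once". The Study treatment section says of the comparator: "In the control group, conventional treatment will be continued, with observation initiated within 8 weeks after enrollment". There is no placebo.

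Three other places matter:

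- Registration and randomization: "Eligible participants will be randomly allocated to the pemafibrate or control groups in a 1:1 ratio".
- Follow up: "At each visit, concomitant medications, cardio-kidney events, and adverse events (AEs) will be verified by the investigators". Nothing restricts this to one arm.
- Conclusion: the study "will evaluate the efficacy and safety of pemafibrate use in patients with hypertriglyceridemia complicated by CKD".

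**The concern.** A percentage with a one-sample interval says how precisely one group's event proportion is known. It does not say how much of that proportion is due to the drug. In patients with CKD followed for 104 weeks, many AEs will come from the underlying disease and its other treatments. The randomized control arm is what separates the two, and it is this trial's main advantage over the single-arm and observational pemafibrate data cited in the Introduction and Discussion.

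The safety-set definition compounds the problem. If only participants who took the study drug are analyzed, the control arm drops out and there is nothing to compare with. If controls are tabulated after all, the reader gets two separate intervals and no interval for the difference. Judging by overlap of such intervals is much stricter than a comparison at the 5% level, so a real excess of general or serious AEs could pass without comment.

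**Working it through.** **1. Does the text give a between-arm estimate?**

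| Item | Stated method | Between-arm estimate? |
|---|---|---|
| Any AE, serious AEs | Counts, percentages, Clopper–Pearson CI | No |
| Drug-related AEs | Same | No; not informative, since controls take no pemafibrate |
| Acute kidney injury, rhabdomyolysis, composite kidney events, composite cardiovascular events (listed under Outcomes in Table 2) | Person-year rates, Kaplan–Meier, Cox hazard ratios (Efficacy analysis) | Yes |
| Liver enzymes, CK, creatinine, eGFR (Table 2) | Mixed models for repeated measures with group differences | Yes |

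The gap is therefore confined to any AE, serious AEs and individual AE terms.

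**2. Arm sizes.** The article states no figure for the safety analysis. Its one design figure, 2200, reproduces closely. With SD 4.0, difference 0.5, one-sided alpha 2.5% and power 80%:

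n per arm = 2 × (4.0/0.5)² × (1.960 + 0.842)² ≈ 1005, so 2010 in total.

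Allowing for 10% drop-out gives 2010/0.9 ≈ 2234, or 2010 × 1.1 = 2211. The arm sizes used below are:

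- planned: 2200/2 = 1100
- enrolled: 2328/2 = 1164
- enrolled less 10%: 1164 × 0.9 ≈ 1048

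The last is a low bound, because a participant who starts treatment and later drops out stays in a safety set defined by one dose.

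**3. A single example (hypothetical counts).** Take 55/1100 (5.0%) on control and 80/1100 (7.3%) on pemafibrate.

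- Clopper–Pearson: 3.8–6.5% and 5.8–9.0%. These overlap.
- Risk difference: 80/1100 − 55/1100 = 2.3 points.
- Newcombe limits use each arm's Wilson interval: control 3.86–6.45%, pemafibrate 5.88–8.96%.
  - Lower = 2.27 − √[(7.27 − 5.88)² + (6.45 − 5.00)²] ≈ 0.3
  - Upper = 2.27 + √[(8.96 − 7.27)² + (5.00 − 3.86)²] ≈ 4.3
- The interval for the difference excludes zero, although the two separate intervals overlap.

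**4. How often this happens.** For each pair of assumed true rates, I summed the exact binomial probabilities over all count pairs where (a) pemafibrate's lower Clopper–Pearson limit exceeds control's upper limit, or (b) the lower Newcombe limit exceeds zero. AE rates are assumptions, since the article gives none.

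| Control vs pemafibrate | Per arm | (a) Intervals separate | (b) Difference CI above 0 |
|---|---|---|---|
| 10% vs 13% | 1048 | 24.7% | 57.7% |
| 10% vs 13% | 1100 | 26.4% | 59.7% |
| 10% vs 13% | 1164 | 28.6% | 62.1% |
| 2% vs 3.5% | 1048 | 21.3% | 55.3% |
| 5% vs 7.5% | 1048 | 31.3% | 65.6% |
| 1% vs 2% | 1100 | 15.9% | 47.4% |
| 5% vs 8% | 1100 | 50.5% | 81.6% |
| 10% vs 15% | 1100 | 76.6% | 94.5% |

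With no true difference (rates of 2%, 5% or 10%), the two intervals separate in either direction in only about 0.3–0.5% of trials, against the nominal 5%.

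**The case against.** **This is an omission from a condensed article.** The full protocol and SAP are not shown, AE table layout is commonly left to them, and exact intervals are a correct description of proportions. This has weight: the SAP may already contain a contrast. But the article is not silent. It names an interval method for AEs and defines the population, and the two together leave no comparison. Elsewhere it does name contrasts: slope differences, mixed-model differences, hazard ratios.

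**The control arm is used for harm.** A reader might infer that the trial makes no comparative safety assessment at all. The documents do not support that. Kidney, muscle, liver and cardiovascular effects all have between-group analyses under Efficacy analysis. This objection stands and limits the point to general and serious AEs.

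**The power figures assume a rule nobody proposed.** A reader might also infer that the plan forfeits about half of the trial's ability to detect excess harm. That does not follow. The article sets no decision rule for AEs and never says intervals will be compared for overlap. If by-arm counts are published, anyone can compute the difference. The gap also depends on the assumed rates: it is much narrower at 10% versus 15% (77% against 95%) than at 1% versus 2% (16% against 47%). The figures illustrate the cost of one way of reading the tables and do not measure a loss built into the plan.

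**Drug-related events cannot be contrasted.** Correct. Controls take no pemafibrate, so those events are left out of the remedy.

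**The safety set may be loosely worded.** The sponsor may intend controls to be included. In that case the definition should say so, and the missing contrast remains.

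**Conclusion.** The point holds within a limited scope. For any AE and serious AEs, the stated method is a one-sample interval on a population defined by receipt of a drug that controls never take, so the plan as written produces no pemafibrate-versus-control estimate. Named outcomes and laboratory measures are not affected.

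This conclusion rests on the text alone. The numerical illustration rests on three further assumptions: AE rates of 10% versus 13%, about 1048 to 1164 participants per arm, and readers who judge by overlap. Under these, an excess would show in about 25–29% of trials, against 58–62% with a risk-difference interval. It is a worthwhile correction to a secondary part of the plan and does not touch the primary analysis.

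**What to change.** 1. Define the safety analysis set to include control participants from the start of observation, alongside pemafibrate participants who took at least one dose.
2. For any AE, serious AEs and common preferred terms, report the pemafibrate-minus-control risk difference with a Newcombe or Miettinen–Nurminen 95% CI. Label these as descriptive, without multiplicity control.
3. Keep the Clopper–Pearson intervals as per-arm description.
4. Leave drug-related AEs as a summary of the pemafibrate arm.

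The cost is a revised definition, a few sentences of SAP wording and one extra column per safety table. No new data collection appears necessary, since AEs are verified at each visit with no stated restriction to one arm. The downside is that, across many terms, some intervals will exclude zero by chance, which is why the descriptive label is needed.
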